##### Patients who voluntarily withdraw from the trial

Every patient has the right to withdraw from the trial in accordance with the Good Clinical Practice (GCP) and informed consent. “Withdrawal” also refers to the loss of a patient after he/she no longer receives the treatment and assessment of the intervention, although he/she does not explicitly propose withdrawal from the study.

If the intervention or control is found to be ineffective, the patient may be unwilling to continue the trial. If the patient proposes to withdraw from the trial to the researcher before returning to the routine treatment.Patients who, due to various other reasons, are unwilling or unable to continue the clinical trial and terminate the trial by offering to withdraw from the trial to the researcher.Although the patients do not explicitly propose withdrawing from the study, they are no longer followed up and are thus lost.

Researchers will aim to learn as much as possible about the reasons for patients’ withdrawal and record them. For example, the perceived curative effect may not be good; patients may not tolerate some adverse reactions; patients may be unable to continue the clinical trial for various reasons, e.g., economic factors; or loss of follow-up without explanation.

##### II. Suspension/termination criteria for the whole trial:

Suspension/termination of the trial means that the entire clinical trial is not completed in accordance with the protocol. The purpose of a trial suspension/termination is to protect patients’ rights and interests, to ensure the quality of the trial, and to avoid unnecessary economic losses.

This trial may be discontinued for the following reasons:

When serious safety problems occur during the trial and the researcher believes that the safety of the patients may be compromised, or when the treatment is found to be too poor or ineffective during the trial to have a clinical value.It is difficult to evaluate the efficacy and/or safety of the treatment because major errors are discovered in the trial protocol or significant deviations in its implementation occur during the trial.The researcher proposes suspension (for example, funding or management reasons, or others).

The researcher will notify the patient, organization responsible for the trial, and Ethics Committee and explain the reasons for discontinuing the trial. The responsible research unit shall notify the investigator, Ethics Committee, and Ministry of Science and Technology before suspending the clinical trial and state the reasons.

#### Relevant concomitant care permitted or prohibited during the trial {11d}

No additional Chinese or Western drugs related to the treatment of the ulcer (vasodilators, such as lipid microspheres prostaglandin injection, beraprost sodium, cilostazol, sagresol hydrochloride, nefuram, butalbital, and hexaketone cocaine, among others; antiplatelet drugs, such as aspirin and clopidogrel; anti-coagulant drugs, such as unfractionated heparin or low-molecular-weight heparin, and oral anti-coagulants; or TCM or proprietary Chinese medicine, topical antibiotics, trimethoprim/sulfamethoxazole, and others, which have the effect of muscle growth and act as astringents in the treatment of sores) should be used during the trial. The same applies to biological treatments (such as stem cell therapy, topical autologous platelet-rich plasma, maggot therapy, cell growth factors, chymotrypsin, and TCM or Chinese herbal tonics with similar functions as the trial treatment).

Drugs that are required to treat comorbidities may be continued. These drugs must be recorded in detail on the case report form, including the name of the drug, dosage, frequency, and duration of use.

Glucose-lowering drugs (oral antidiabetics and insulin) will be selected according to the patient’s blood glucose level at the time of enrollment and treatment regimen. Except for uncontrolled hyperglycemia, the type of glucose-lowering drug or insulin regimens of patients will remain unchanged, although the dosage will be adjusted according to blood glucose levels. Blood glucose levels and glucose-lowering drug doses will be recorded in a timely and detailed manner on the case report form. Patients whose blood glucose levels cannot be normalized within a week will be discontinued from the trial.

### Outcomes {12}

#### Primary outcome

The wound coverage with granulation tissue will be the primary outcome. The development of granulation tissue will be assessed as follows:

$$\text{Wound coverage rate} = \text{The wound area covered by granulation tissue}\, (\text{mm}^{2})/\text{Whole wound area}\, (\text{mm}^{2}) \times 100\%$$

We will use three-dimensional scanning to obtain the wound surface topography and the inSight® platform (eKare, Inc., Fairfax, VA, USA) to identify the different tissue types and to measure the areas covered by them.

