##### I. Termination of a patient’s participation based on the researcher’s decision

The researchers may decide to withdraw enrolled subjects from the study when they establish that they are not suitable to continue the study for any of the following reasons:

During the trial, clinical endpoints (such as the need for surgery) are reached.The patient undergoes surgical treatment other than debridement of the ulcer site.During the clinical trial, patients experience complications or physiological changes that make it inappropriate for them to continue to receive treatment within the trial.Use of other prohibited treatments or drugs that affect the assessment of the efficacy and safety of the intervention.If serious adverse events occur during the trial, the researcher may decide whether to suspend the trial.Poor compliance of the patients that results in the failure of 80% of the prescribed dosage of topical drugs (except cured patients) or the failure of 120% of the prescribed dosage.

Subjects who will be withdrawn from the trial will undergo a final visit to evaluate each efficacy indicator and to complete a safety assessment.

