#### Secondary outcomes

As secondary outcomes, we will determine the wound healing rate, amputation rate and extent, granulation time, and Maryland Foot Score.

Wound healing rate = (Original wound area - unhealed wound area)/Original wound area ×100%.Amputation extent: A extensive amputation refers to an amputation above the ankle, while a limited amputation refers to an amputation below the ankle. The amputation level will be identified in a multidisciplinary team of vascular surgeons and orthopedic foot and diabetes specialists according to the results of the lower limb angiography.Granulation time (days): The period of time within which new granulation tissue appears within the wound.The Maryland Foot Score will be determined to evaluate foot function, including the presence or absence of pain. The maximum score is 100 points, > 89 points indicate excellent function, 75–89 points good function, 50–74 average, and < 50 points poor function.

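### As written, the granulation-coverage formula gives a closed wound no favourable score and can fall as a wound epithelialises, because the denominator is undated and epithelialised area does not count as covered

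*Protocol article*

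**What the plan says.** Under Outcomes {12}, Primary outcome, the protocol article states that "The wound coverage with granulation tissue will be the primary outcome". It computes this as "The wound area covered by granulation tissue" over "Whole wound area", in mm², times 100%. A scanning platform is used "to identify the different tissue types and to measure the areas covered by them". The section does not tie the denominator to a visit, does not say that epithelialised area counts as covered, and gives no value for a closed wound.

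The healing rate under Secondary outcomes does fix its denominator: "Wound healing rate = (Original wound area - unhealed wound area)/Original wound area". It equals 100% at closure.

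Other relevant places in the article:
- Background and rationale {6a} says the combination supports regrowth of both granulation and epithelium.
- The discontinuation criteria {11b} set a minimum-use rule for the topical drugs with the carve-out "except cured patients".
- Eligibility criteria {10} admit target ulcers of 1 to 20 cm².
- Table 1 schedules both the coverage rate and the healing rate at day 0, day 14 and day 28.
- Data management {19} requires at least one post-treatment primary measurement for the full analysis set and uses last observation carried forward for incomplete courses.

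**The concern.** Granulation is an intermediate stage. As a wound heals, granulating area is replaced by epithelium, and the formula stops counting it. A primary outcome should not get worse when the patient gets better. Here it can, and at full closure it has either no value or the lowest possible value.

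If one arm epithelialises more, its mean coverage is pulled down by that success. Since the stated mechanism of the test treatment includes epithelial growth, the treatment arm is the one at risk if the treatment works as described. The primary outcome and the healing rate could then point in different directions. Leaving the denominator open also allows two different primary analyses, and choosing between them after seeing data in a non-blind trial would itself be a source of bias.

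**Working it through.** The plan gives no expected value for this ratio, so there is no figure to reproduce. The effectiveness rates of 50% and 71% in the sample-size section are not linked to the ratio by any threshold and cannot be used to size the problem. The check is on how the formula behaves.

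**Notation.** W0 = day-0 wound area; W = current open area; G = granulating area; B = W − G = open area still bare or necrotic; e = granulating area that epithelialises.

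**Closed wound** (W = 0, G = 0):
- Current-area reading: 0/0, undefined.
- Day-0 reading: 0/W0 = 0%.
- Healing rate: (W0 − 0)/W0 = 100%.

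**Epithelialisation with B unchanged:**
- Current-area reading: G/W becomes (G − e)/(W − e). The change is e(G − W)/[W(W − e)], which is negative whenever G < W and zero when G = W. Equivalently, the score is 1 − B/W, so it falls whenever the open area shrinks by a larger proportion than the bare area does.
- Day-0 reading: G/W0 becomes (G − e)/W0, which is always lower.

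**Illustration.** W0 = 1000 mm² is assumed; it lies within the eligible 100 to 2000 mm².

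| State | W | G | B | G/W | G/W0 | Healing rate |
|---|---|---|---|---|---|---|
| 1. Granulating, no epithelium | 1000 | 800 | 200 | 80% | 80% | 0% |
| 2. 300 mm² epithelialised | 700 | 500 | 200 | 71.4% | 50% | 30% |
| 3. 600 mm² epithelialised | 400 | 200 | 200 | 50% | 20% | 60% |
| 4. Fully granulated, 400 open | 400 | 400 | 0 | 100% | 40% | 60% |
| 5. Nearly closed | 50 | 50 | 0 | 100% | 5% | 95% |
| 6. Closed | 0 | 0 | 0 | 0/0 | 0% | 100% |
| 7. Unchanged size, half granulated | 1000 | 500 | 500 | 50% | 50% | 0% |

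From state 1 to state 3 the same wound improves from 0% to 60% healed while its primary score drops by 30 points (current area) or 60 points (day-0 area). State 3 then scores the same as the unhealed state 7, or 30 points below it. States 4 and 5 show the limit of the problem: on the current-area reading a fully granulated wound holds 100% until it closes.

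**Possible effect on the comparison, day-0 reading only.** Scoring closed wounds 0 instead of 100 lowers each arm's mean by 100 × its closure proportion, so the between-arm difference shifts by 100 × the difference in closure proportions. These proportions are assumptions. At 15% versus 5% closed, the means fall by 15 and 5 points and the difference loses 10 points. At equal closure it loses none, and at a 5-percentage-point gap it loses 5.

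**Current-area reading.** A wound closed at both day 14 and day 28 has no defined post-treatment value, so its place in the full analysis set is unclear. A wound closed only at day 28 might keep its day-14 value if coded as missing. The article settles neither case.

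**The case against.** The healing-rate formula names the original area when the baseline is meant, whereas the primary formula speaks of the whole wound next to a scan that separates tissue types. That contrast favours the current-area reading, on which the 0% score and the largest drops disappear. This stands. What remains is 0/0 at closure and a fall that occurs only while some bed is not granulated.

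A reader might infer that cures within four weeks are forecast and that the problem is therefore certain to matter. The documents do not support that. The mention of cured patients is an exemption in a compliance rule, no closure rate is given, and the population has Wagner grade 3–4 ulcers with exposed tendon, in whom full closure by day 28 may be uncommon. Partial epithelialisation is the more general route, but its frequency is not given either.

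A reader might also infer that the primary time point is missing. Table 1 closes out at day 28, and the carry-forward rule runs to the final observation, so day 28 is the evident visit.

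Finally, coding rules are often left to a full protocol or analysis plan. That would excuse silence on a coding detail. It does not cover a stated formula that, followed literally on either reading, gives a healing wound an unsuitable value.

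**Conclusion.** The point holds in limited form. The formula leaves its denominator undated, gives a closed wound no favourable value on either reading, and can move against the healing rate in the same patient: always on the day-0 reading when granulation epithelialises, and on the current-area reading while any bare or necrotic bed remains.

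The algebra needs no assumption beyond granulation being replaced by epithelium. The table's wound states and the closure proportions are illustrative. The size and direction of any effect on the trial result are unknown, and depend on how much the arms differ in epithelialisation and closure. It would go too far to say that the outcome never rises with benefit, that the result will be reversed, or that healed patients will be lost from the analysis.

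**What to change.** Before data are analysed and without reference to arm, define the primary outcome at day 28 as

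100% × (1 − remaining non-granulated open area / day-0 target-ulcer area), bounded at 0–100,

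where the non-granulated area is bare tendon or necrotic bed. Epithelialised and contracted area then count as covered, and a closed wound scores 100%. The seven states in the table score 80, 80, 80, 100, 100, 100 and 50%, so epithelialisation no longer lowers the score.

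Adding epithelium to the numerator over the day-0 area is not an equivalent repair, because it ignores contraction. Take day-0 area 10, contraction 3, epithelium 2, granulation 4, bare 1. That version gives (4 + 2)/10 = 60%, whereas the proposed one gives 1 − 1/10 = 90%.

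At a minimum, name the denominator and score closed wounds as 100%. Report granulation over current open area as a supportive analysis, since it stays closest to the stated aim of covering tendon with granulation.

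**Cost.** No new measurement is needed. If unhealed area in the healing rate H means current open area, the new score (before bounding) is 1 − (1 − H)(1 − C) where C is coverage on the current area, or H + C where C is coverage on the day-0 area. State 2 gives 1 − 0.7 × 0.286 = 80% and 30% + 50% = 80%. Closed wounds, where C may be undefined, are set to 100%.

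The real cost is a late change to a primary outcome in a non-blind trial whose recruitment was expected to end in December 2022, before the article appeared in October 2023. It should be dated, justified and reported as such.

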#### Secondary outcomes

As secondary outcomes, we will determine the wound healing rate, amputation rate and extent, granulation time, and Maryland Foot Score.

Wound healing rate = (Original wound area - unhealed wound area)/Original wound area ×100%.Amputation extent: A extensive amputation refers to an amputation above the ankle, while a limited amputation refers to an amputation below the ankle. The amputation level will be identified in a multidisciplinary team of vascular surgeons and orthopedic foot and diabetes specialists according to the results of the lower limb angiography.Granulation time (days): The period of time within which new granulation tissue appears within the wound.The Maryland Foot Score will be determined to evaluate foot function, including the presence or absence of pain. The maximum score is 100 points, > 89 points indicate excellent function, 75–89 points good function, 50–74 average, and < 50 points poor function.

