### Eligibility criteria {10}

#### Inclusion criteria

Patients who meet the following criteria will be included:

Diagnostic criteria for diabetic foot disease and Wagner grade 3–4 ulcers with exposed tendon tissue;Age between 18 and 85 years;Fasting blood glucose ≤ 10 mmol/L;Targeted ulcer debridement area between 1 and 20 cm^2^ (for patients with multiple lesions, the largest ulcer will be the target lesion);An ankle-brachial index ≥ 0.5 on the side of the limb with the ulcer;The ulcer has blood, pus, or sticky secretion;Voluntary participation and signing of an informed consent form.

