#### Sample size {14}

The sample size was calculated using Pass 11.0 software (NCSS Statistical software https://www.ncss.com/software/pass). Based on a preliminary review of the literature and the clinical practice and experience of the Second Affiliated Hospital of Tianjin University of Traditional Chinese Medicine in the treatment of diabetic foot ulcers, the control group is expected to have an effectiveness of 50%, and the treatment group of 71%. Postulating a patient ratio of 1:1 between groups and an alpha of 0.05 on both sides, 72 patients would be required in each group. Assuming a 20% loss to follow-up, we calculated a number of 90 patients in each group and a total of 180 patients as the target sample size.

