#### Sequence generation {16a}

Using a central random system and minimization algorithm, the allocation probability of the target group will be calculated for each enrolled patient for them to be assigned to the most suitable treatment group and ensuring a balance of control factors between the groups. The controlling factors are (1) ulcer location (plantar, dorsum of foot, or toe), and (2) ABI evaluation index (> 0.7, and ≤ 0.7).

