### Statistical methods for primary and secondary outcomes {20a}

Statistical description.Detailed description of cases of withdrawal and censoring, including the time and reason for censoring.Descriptive statistics: Based on their distribution, data will be presented as either the mean and standard deviation, or the median with maximum, minimum, and confidence interval, or the number and frequency (%), among others.Statistical inference method.Measurement data: The paired t-test, analysis of variance, the rank-sum test, signed rank-sum test, and the median test will be used.Counting data: The chi-square test, Fisher exact test, and others will be used; grade data will be analyzed using the ridit test and the Cochran–Mantel–Haenszel test.Primary outcome analysis: Per protocol set analysis and full analysis set analysis will be performed. The Cochran-Mantel-Haenszel test will be used for multicenter counts and analysis of covariance for measures. For the confounding factors that are difficult to control or are uncontrolled before allocation, the least-squares means of the analysis of covariance and their 95% confidence limit or logistic regression will be used as covariates to determine the between-group efficacy.Two-sided difference tests will be used to assess statistical differences, and a difference with a p-value of ≤ 0.05 will be considered to be statistically significant.

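### The wound healing rate is a percentage area reduction in ulcers of 1 to 20 cm², but day-0 area is not fixed as a covariate for its comparison, which may cost precision

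*Protocol article*

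**What the plan says.** Four parts of the protocol article bear on this point.

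- **Secondary outcomes.** The wound healing rate is the percentage form of "Original wound area - unhealed wound area)/Original wound area". Each patient's own starting area is the denominator. Table 1 schedules the measurement on day 0, day 14 and day 28.
- **Inclusion criteria.** "Targeted ulcer debridement area between 1 and 20" cm² is required, so the limits are 20-fold apart.
- **Sequence generation {16a}.** "The controlling factors are (1) ulcer location (plantar, dorsum of foot, or toe), and (2) ABI evaluation index". Ulcer area is not among the factors.
- **Statistical methods for primary and secondary outcomes {20a}.** For measurement data in general: "The paired t-test, analysis of variance, the rank-sum test, signed rank-sum test, and the median test will be used". None of these, as listed, uses a baseline covariate. After the label for the primary outcome analysis comes "The Cochran-Mantel-Haenszel test will be used for multicenter counts and analysis of covariance for measures", followed by "For the confounding factors that are difficult to control or are uncontrolled before allocation, the least-squares means of the analysis of covariance". No covariate is named, and no particular test is assigned to the wound healing rate.

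**The concern.** Dividing by the original area removes the influence of size only if wounds shrink in proportion to their area. If the wound edge moves inward by a distance unrelated to size, the division creates a size dependence: a small ulcer scores much higher than a large one for the same movement. The score also has no lower bound, so a small ulcer that enlarges can score far below zero.

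In that case an unadjusted test puts the spread due to starting size into its error term, and a real effect on healing is easier to miss. A chance difference in ulcer size between arms also stays in the estimate, because size is not balanced by the minimization. The value that would absorb this spread is already measured in every patient, as the denominator of the outcome.

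**Working it through.** **Inputs from the document.** Area limits of 1 and 20 cm²; the healing-rate formula; minimization on location and ABI only; 72 evaluable patients per group, two-sided alpha 0.05.

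**The plan's own figure.** There is none for this outcome: no standard deviation, effect size or correlation with area. The sample size section rests on a different quantity: "the control group is expected to have an effectiveness of 50%, and the treatment group of 71"%. Its 72 per group, inflated as 72/(1 − 0.20) = 90, is used here only as the number analysed.

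**Step 1: geometry (assumes circular wounds).** With radius r = √(A/π) and edge advance d, healing = 1 − (r − d)²/r².

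| Area | r | d = +2 mm | d = −2 mm |
|---|---|---|---|
| 1 cm² | 5.64 mm | 58.3% | −83.5% |
| 5 cm² | 12.62 mm | 29.2% | −34.2% |
| 10 cm² | 17.84 mm | 21.2% | −23.7% |
| 20 cm² | 25.23 mm | 15.2% | −16.5% |

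**Step 2: gain as a function of the correlation.** Let ρ be the correlation between (log) day-0 area and the healing rate. Adjustment changes the residual SD to SD·√(1 − ρ²). Assume a standardized effect of (1.960 + 0.842)·√(2/72) = 0.467, which gives 80.0% power unadjusted. Adjusted power is about Φ(2.802/√(1 − ρ²) − 1.960), and the number per group for unchanged power is 72(1 − ρ²).

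| ρ (absolute) | Power adjusted | n per group for 80% |
|---|---|---|
| 0 | 80.0% | 72 |
| 0.2 | 81.6% | 69.1 |
| 0.3 | 83.6% | 65.5 |
| 0.4 | 86.4% | 60.5 |
| 0.5 | 89.9% | 54.0 |
| 0.6 | 93.8% | 46.1 |

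**Step 3: what ρ could be.** This depends on the assumed healing model. Under proportional shrinkage ρ is 0. With a mean edge advance of 0.3 cm over four weeks and a coefficient of variation from 1.0 down to 0.3, ρ with log area runs from −0.40 to −0.82. The share of spread due to size (ρ²) therefore runs from 0% to 0.82² = 67%.

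**Step 4: simulation under edge advance.** Assumptions: 72 per arm, log-uniform area from 1 to 20 cm², normally distributed edge advance, 3,000 trials per scenario. The comparison is a t-test against analysis of covariance with log day-0 area.

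| Control mean / difference / SD (mm) | Unadjusted | Adjusted | Gain (points) |
|---|---|---|---|
| 2 / 0.7 / 1.5 | 64% | 75% | 11 |
| 3 / 0.9 / 1.5 | 72% | 93% | 21 |
| 3 / 0.6 / 1.0 | 52% | 92% | 40 |
| 2 / 1.0 / 2.5 | 57% | 60% | 3 |

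A repeat run gave 63 to 73%, 74 to 93%, 55 to 93% and 56 to 60%. The rank-sum test, also on the protocol's list, gave 62%, 72%, 52% and 55% there, so it does not recover the loss. The variance of the adjusted estimate was 0.94 to 0.37 of the unadjusted one. Type I error was about 5% for both methods.

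**Step 5: the case where size does not matter.** With percentage reduction independent of size (means 40 and 55, SD 32), power was 80.1% unadjusted and 79.6% adjusted, a cost of 0.5 point.

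**Step 6: chance imbalance.** The SD of log-uniform area is ln(20)/√12 = 0.865, so the SD of the between-arm difference in mean log area is 0.865·√(2/72) = 0.144. With slopes of about −11 to −19 percentage points per log unit, a 1-SD imbalance moves the unadjusted difference by about 1.6 to 2.7 points. With SD 32, the standard error of that difference is 32·√(2/72) = 5.3 points.

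**The case against.** The strongest objection is that the article does not say the wound healing rate will be tested without day-0 area. It assigns no test to this outcome. The statistical section is headed for primary and secondary outcomes, and its covariate sentence covers factors not controlled before allocation; ulcer area would qualify. Covariate lists are also commonly left to an analysis plan, which is not shown. This stands in part: a reader might infer that adjustment is ruled out, and the text does not support that. But the covariance sentence follows the label for the primary outcome analysis and admits covariates as unnamed confounders. The methods listed for measurement data in general are unadjusted. The point is therefore about the methods the article does list, and not only about a missing detail.

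A reader might also infer that ulcer size does drive much of the spread. The document gives no figure for that. The eligibility limits are bounds and not a distribution, the outcome already divides by area, and the share due to size runs from 0% to about 67% with the assumed model. The largest simulated gain comes from the smallest assumed SD.

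Nor is the comparison biased. Under randomization the unadjusted difference is valid, and its standard error already reflects chance imbalance; the 1.6 to 2.7 points are modest against 5.3. The trial is not sized on this outcome, so no stated power is affected.

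Finally, the listed rank-sum and median tests already limit the weight of extreme negative scores. That is correct, but they do not remove the spread due to size. Adjustment on the raw scale, in turn, does not bound the tail, hence the rank-based sensitivity analysis below.

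**Conclusion.** The point holds as one of efficiency and prespecification. The article defines a size-dependent type of score, admits a wide range of sizes, does not balance on size, and lists only unadjusted tests for measurement data outside the primary outcome analysis, without fixing day-0 area as a covariate. If wounds heal by edge advance, starting size can account for a material share of the spread, and the unadjusted test loses precision without being biased.

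The gain cannot be quantified from the document. It is about 3 to 40 points of power under the assumed edge-advance models (circular wounds, log-uniform areas, 72 per arm), and a loss of about 0.5 point if percentage reduction does not depend on size. That asymmetry, and not any demonstrated loss, is the reason to act. The stronger readings, that size is known to dominate this outcome or that the randomized comparison is distorted, are not supported.

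**What to change.** Keep the wound healing rate as defined and add one sentence to the statistical methods: the between-arm comparison at day 28 will be made by analysis of covariance with log(day-0 ulcer area) as a fixed covariate, reporting the adjusted difference with its 95% confidence interval. Add a rank-based version as a sensitivity analysis for the negative tail. If adjustment is already intended through the existing covariate sentence, state that it applies to this outcome and name the covariate.

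The cost is one degree of freedom and no new data, since the area is already measured on day 0. Settle the wording before the outcome data are compared by arm, so that the covariate is not chosen after the results are seen.
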